## Abstract

**Background:**

Depression in older adults is a serious health problem with a poor prognosis. There is a need for indicated preventive psychological interventions for older adults, that show to be promising in preventing depressive disorders.

**Methods/design:**

This manuscript describes the design of a study evaluating 'Looking for Meaning', a newly developed prevention course for older adults with depressive symptoms, based on life-review. Both clinical and economic effectiveness are evaluated in a pragmatic randomized controlled trial. The control condition of this 12-session preventive intervention is a 20-minute video movie. The primary outcome is symptoms of depression at post-treatment and follow-up (6 months after post-treatment). Secondary outcomes are symptoms of anxiety, satisfaction with life, mastery, reminiscence styles, quality of life, and health care costs. An additional result of this study is the insight into the working elements of the course, provided by the qualitative study. The qualitative data, mainly based on 20 open-ended interviews with participants, are to be analyzed with an emphasis on newly emerging insight.

**Discussion:**

This study will add to the existing scientific knowledge in several ways, especially by also including an economic evaluation and a qualitative study to gain insight into the working mechanisms of the course, both rather new in the field of life review. Positive results of this study will make an evidence-based intervention to improve public health among older people available.

**Trial registration:**

Current Controlled Trials Ltd, ISRCTN66645855

## Background

Depression in older adults is a serious health problem with a poor prognosis [1]. Major depression occurs in approximately 1,8% of the general population aged 55 and over, and minor depression in another 9,8% [2]. Considering the high prevalence rate of depressions in people aged 55 and older, there is a need for effective, low-threshold preventive interventions tailored to older adults.

Indicated prevention starts tackling disorders at the symptom level [3]. In contrast with universal prevention (general; aims at no specific target group) and selective prevention (focuses on risk groups with no symptoms yet), indicated prevention directly deals with the major risk factor for developing a full-blown depression particularly in old age: the presence of some of the depressive symptoms [4]. A recent meta-analysis shows that psychological interventions for older adults with depressive symptoms are indeed promising in preventing depressive disorders [5].

Several psychological interventions are currently available for reducing depression symptoms in older people, including psycho-educational approaches, cognitive behavioral therapy, psychodynamic therapy, and interpersonal therapy [6-8]. The use of life review is gaining popularity, because this type of intervention may pertain to older adults in particular. Meta-analyses have shown that life-review has significant and substantial effects on both depression and psychological well-being [9,10].

The first to emphasize the importance of life review in old age was Butler [11]. He observed that older adults increasingly review their lives as they grow older, and that they seem to do so naturally. He considered life review the expression of a universal mental process reflecting the need to come to terms with one's life when the end is approaching. Since Butler's observations, scientists and clinicians have shown a growing interest in life review, both as a phenomenon and as a method of treatment for older adults with depression [12-14].

Life review, can fulfill various functions for the individual; people review their lives for different reasons and with different motivations. An individual may apply more than one style. A particular reminiscence style is assumed to relate with more or less favorable outcomes in terms of mental health [15]. Integrative life review is most well-known, and implies an evaluation of one's past in order to accept negative events, resolve past conflicts, identify continuity of past and present, and, eventually, find meaning in life [16]. However, for some older adults life review can be depressing or burdensome. Especially when they tend to focus on negative past experiences, life-review may have a self-subversive rather than positive impact. Life review prompted by 'negative' motivations, such as boredom reduction or bitterness revival, are associated with undesirable clinical outcomes (e.g., anxiety, a low sense of self efficacy, dissatisfaction with life, or depressive symptoms). Transforming these styles and supporting 'positive' reminiscence may therefore promote older adults' mental health.

We developed an indicated prevention course, called 'Looking for Meaning', which is a well-structured type of life review with the underlying assumptions that reminiscence styles influence coping with depressive symptoms and can be changed or transformed by means of an intervention [17]. This course may prevent depressive symptoms from developing into a major depression. A pilot study with a previous version of this course exploring the impact of this approach showed promising results for the mental health of older adults [18]. A next step is to carry out a randomized controlled trial (RCT).

In this paper the design of the RCT on (cost)effectiveness of life review for older adults will be described. In order to be able to explicitly relate reminiscence styles to clinical outcomes, we also measured reminiscence styles and -functions. In addition, a qualitative study was designed to gain an insight into what participating in this course meant to the older adults and how life review in particular might have influenced coping with depression and other mental health issues in their lives. The specific research questions these studies aimed to answer were:

1. Does the prevention program Looking for Meaning lead to a significant reduction of depressive symptoms and a significant enhancement of wellbeing, satisfaction with life, and quality of life in elderly people with depressive symptoms, in comparison with a no-treatment control group?

2. Which prognostic factors (demographic, clinical symptoms, mastery), in combination with the intervention, predict lower or higher effects on depressive symptoms, wellbeing, satisfaction with life and quality of life?

3. What is the incremental cost-utility in the treatment group as compared to the control group?

4. Which are the working components of the intervention, leading to reduction of depression and enhancement of wellbeing, mastery and satisfaction with life, according to the participants?

## Methods/Design

### Design

To evaluate the (cost)effectiveness of the life review course 'Looking for Meaning', we carry out a pragmatic randomized controlled trial (RCT) with a cost effectiveness analysis (CEA). Participants are randomly assigned to either the 12-session prevention course or the control condition, the twenty-minute video movie entitled 'The Art of Growing Older'. In addition, we conduct a qualitative interview- and observational study to gain insight into how participants apply and use life review, how they think it helps them coping with depression, and to learn about which course elements have or have not worked for them. The research has been judged and ethically approved by the METiGG, a medical-ethical committee for research in mental health care settings in the Netherlands.

### Participants

Participants are recruited via advertisements in local and national newspapers, magazines targeted at an older audience, or selected with the help of professionals affiliated to one of eleven regional institutes for mental health care in both rural and urban areas of the Netherlands participating in this study. These mental health care institutes support the participant recruitment and -intake, make available the professionals needed, and eventually take care of organizing and offering the course within their institute.

In order to participate in this study, participants have to show slight to moderate depressive symptoms; people diagnosed with a major depression are excluded, as well as people showing no symptoms at all. The intended population is aged 55 and up, as the course was developed for older adults. People who respond, are screened for depressive symptoms by mental healthcare professionals (e.g., a psychologist or a therapist). People scoring 24 or higher on the Center for Epidemiological Studies Depression Scale (CES-D), are further examined with the Mini International Neuropsychiatric Interview (MINI) in order to decide whether a major depression is present or not [19-21]. People with scores below 5 are excluded from the study as well, because improvement is hardly possible. People eligible to participate are asked to complete the consent form.

### Randomization

Participants are randomly assigned to either of the two research conditions by means of a centrally conducted randomization stratified for gender. This means the randomization takes place at the research institute (Netherlands Institute of Mental Health and Addiction), independent of the participating institutions; they receive the outcome of the procedure in the regular mail and are to schedule the participants accordingly.

### Sample size

In order to demonstrate a standardized effect size of 0.35 (a medium-sized effect [22]) a minimum of eighty participants in each condition is required at the time of the follow-up measurement (t2), based on a statistical power (1-beta) of 0.80, a one-sided test, and a conventional alpha of 0.05 (power calculation in Stata 7.0). Anticipating a drop-out of 20% between t0 and t2, slightly over one hundred participants per condition were included at t0, the baseline measurement.

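### Eighty per arm at t2 gives about 71% power for an effect of 0.35, not the stated 80%; the printed inputs require about 101 per arm

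*Protocol article*

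**What the plan says.** The Sample size section gives a complete set of inputs: a standardized effect of 0.35, a calculation "based on a statistical power (1-beta) of 0.80", and "a one-sided test, and a conventional alpha of 0.05 (power calculation in Stata 7.0"). From these it concludes that "a minimum of eighty participants in each condition is required at the time of the follow-up measurement (t2"). It then sets enrolment: "Anticipating a drop-out of 20% between t0 and t2, slightly over one hundred participants per condition were included at t0".

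The section names no baseline correlation, covariate adjustment or repeated-measures assumption. The Analyses section names no baseline-adjusted model either. It describes effect sizes as mean changes divided by the pretreatment standard deviation, with the between-group effect as the difference between the two arms' values.

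**The concern.** The article prints both the inputs and the result, so a reader can check one against the other, and they disagree. The required number exceeds the stated one by about a quarter (101/80 = 1.26), which is too much for rounding or for a difference between normal and t-based formulas.

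The error favours the trial. The abstract makes depressive symptoms at post-treatment and at follow-up the primary outcome, and follow-up (t2) is the time point used for sizing. If readers believe the power at t2 is 80% when it is nearer 71%, they will take a null result as stronger evidence against an effect of 0.35 than it is.

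**Working it through.** **Inputs** (all from the Sample size section): d = 0.35; power 0.80, so z = 0.842; one-sided alpha 0.05, so z = 1.645; equal arms; 80 per arm at t2; 20% drop-out from t0 to t2; slightly over 100 per arm at t0.

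**1. The plan's drop-out step.** 80 / (1 − 0.20) = 100 per arm at t0. This agrees with the stated enrolment, so 80 is the intended number analysed and not a misprint.

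**2. The plan's required number.** For two independent means, n per arm = 2 × (z for alpha + z for power)² / d².

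- n = 2 × (1.645 + 0.842)² / 0.35² = 100.9, so 101 per arm.
- The t-test version gives 101.6, so 102 per arm.
- The stated 80 is not reproduced. The shortfall is 21 to 22 completers per arm.

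**3. Power at 80 per arm.** Power = Φ(d × √(n/2) − 1.645).

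- Φ(0.35 × √40 − 1.645) = 0.715; the t-test version is 0.712.
- Type II risk is therefore about 29%, against the stated 20%.

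**4. Effect detectable with 80% power at 80 per arm.** (1.645 + 0.842) × √(2/80) = 0.393, about 0.39 (0.395 by the t-test).

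**5. Enrolment that the inputs imply.** 101 / 0.80 = 126.25, so 127 per arm at t0; starting from 102 it is 128. At 100 per arm analysed, power would be 79.7%. The t0 number therefore roughly meets the requirement only if nobody drops out.

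**6. Other readings of the same inputs.**

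| Change made | n per arm |
|---|---|
| Two-sided test | 129 (power at 80 is 60%) |
| Effect 0.40 instead of 0.35 | 78 |
| Power 0.70 instead of 0.80 | 77 |
| One-sided alpha 0.10 | 74 |

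The two-sided test widens the gap. The other three come near or below 80, but each contradicts a printed input.

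**7. What unstated correlation would make 80 correct?** The article gives no baseline-to-outcome correlation r, so r is an assumption here. The effect is held at 0.35 baseline standard deviations, with equal variances.

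- ANCOVA: n = 100.9 × (1 − r²). Setting n = 80 gives r = 0.46.
- Change scores: n = 100.9 × 2(1 − r). Setting n = 80 gives r = 0.60.

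| Assumed r | ANCOVA n per arm | Change-score n per arm |
|---|---|---|
| 0.3 | 92 | 142 |
| 0.4 | 85 | 122 |
| 0.5 | 76 | 101 |
| 0.6 | 65 | 81 |
| 0.7 | 52 | 61 |

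Averaging the two post-baseline measurements, without using baseline, would give 80 if they correlate at about 0.585. The text does not describe that analysis, and it would not be a t2 comparison.

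**The case against.** The strongest reply is that the section never says the calculation was for an unadjusted comparison at one time point. CES-D is measured at intake, t1 and t2, and the Analyses section works with changes from baseline. On a change-score test the 71% is itself conditional: with 80 per arm, power is about 59% at r = 0.3, 71.5% at r = 0.5, 80% at r = 0.6 and 89% at r = 0.7. With ANCOVA it is about 82% at r = 0.5. An article may also leave such an assumption to a full protocol that is not shown.

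Part of this stands. The article cannot show that the trial's real power is 71%; that figure is the power its printed inputs imply. But those inputs are presented as the basis of the calculation, no correlation is among them, and no baseline-adjusted analysis is described. Change scores do not reliably help either: below r = 0.5 they need more than 101 per arm. The correlation would have to hold from t0 to t2, which is nine months (3 + 6), and the article offers no support for a value.

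Two smaller points also have some force. The article does not plan to read a null result as ruling out 0.35, so that harm lies with readers. And both 0.35 and 0.39 fall in the article's own moderate band of 0.33–0.55. Neither makes the stated power correct. Nor does the planned regression imputation, since filling in missing values does not restore the information lost with the drop-outs.

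**Conclusion.** The sample size statement is wrong as written. Under the stated inputs, 101 to 102 per arm are needed at t2 and about 127 to 128 at t0. The stated 80 per arm gives about 71% power for 0.35, or 80% power for 0.39.

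This assumes a two-sample comparison of means at t2 with independent observations and no gain from baseline adjustment, which is all that the printed inputs support. A baseline correlation of about 0.46 (ANCOVA) or 0.60 (change scores) would make 80 adequate, but the article states neither.

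**What to change.** Rewrite the Sample size paragraph to say that 80 completers per arm give about 71% power for a standardized effect of 0.35, or 80% power for 0.39, with a one-sided test at 0.05. The section describes inclusion in the past tense, so no further enrolment is asked for.

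The claim of 80% power for 0.35 can stay only if the calculation really used baseline information. In that case the paragraph should name the analysis and the assumed correlation (at least 0.46 for ANCOVA, about 0.60 for change scores), and the Analyses section should name the same analysis. A correlation should not be chosen afterwards to recover the number 80.

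The cost is one paragraph and a less favourable stated power or detectable effect. Data collection does not change.

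### The sample size rests on an unexplained one-sided 0.05 test, and even on those terms 80 per arm gives about 71% power, not 80%

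*Protocol article*

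**What the plan says.** The Sample size section sets the target this way: "In order to demonstrate a standardized effect size of 0.35", the plan needs at least 80 participants per condition at t2, "based on a statistical power (1-beta) of 0.80", "a one-sided test, and a conventional alpha of 0.05". It then allows for loss to follow-up ("Anticipating a drop-out of 20% between t0 and t2") and reports that "slightly over one hundred participants per condition were included at t0". No reason is given for testing in one direction only.

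This is the only place in the article that mentions sidedness or alpha. The Analyses section describes imputation, standardized effect sizes and a bootstrapped cost-effectiveness ratio. It names no hypothesis test for the CES-D. Research question 1 asks whether the course leads to a significant reduction of depressive symptoms compared with the control group.

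The Background says of the method under test: "However, for some older adults life review can be depressing or burdensome". It adds that, particularly when people dwell on negative experiences, "life-review may have a self-subversive rather than positive impact".

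**The concern.** A one-sided test towards benefit suits a setting where an effect in the other direction is implausible or would not matter. The Background does not describe such a setting. It ties negatively motivated life review to undesirable outcomes that include depressive symptoms, which are the primary outcome here.

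Two consequences follow if the one-sided 0.05 rule is applied to the primary contrast. A result with a two-sided p value between 0.05 and 0.10 in the favourable direction would count as a significant benefit. A result in the unfavourable direction could not be declared, however large. The Discussion says that positive results will make an evidence-based intervention available, so this threshold carries the trial's main claim.

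The required number is a separate matter. It has to follow from the stated inputs whichever test is chosen. If it does not, the stated 80% power is not what the design delivers.

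**Working it through.** **Inputs from the Sample size section:** d = 0.35 (SD = 1), power 0.80, alpha 0.05 one-sided, equal arms, 80 per arm at t2, drop-out 20%. **Normal quantiles:** 1.645 (one-sided 0.05), 1.960 (two-sided 0.05 or one-sided 0.025), 0.842 (power 0.80).

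1. **The plan's own figure.** n per arm = 2(z_alpha + z_power)² / d² = 2(1.645 + 0.842)² / 0.35² = 100.9, so 101. The noncentral t calculation gives 101.6, so 102. The stated 80 is not reproduced. Other settings do not give 80 either: one-sided 0.10 gives 74 and two-sided 0.05 gives 129 (normal approximation).

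2. **The drop-out step.** 80 / (1 − 0.20) = 100 per arm at t0. This agrees with the article, so the discrepancy lies in the 80 itself.

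3. **Power at 80 per arm, one-sided 0.05, unadjusted.** d·√(n/2) = 0.35 × √40 = 2.214, and Φ(2.214 − 1.645) = 0.715. The noncentral t gives 0.712.

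4. **Power at 80 per arm, two-sided 0.05, unadjusted.** Φ(2.214 − 1.960) = 0.600. The noncentral t gives 0.595. For 80% power, 129 per arm are needed (noncentral t: 130).

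5. **Effect detectable with 80% power at 80 per arm.** (z_alpha + z_power)·√(2/80) gives 0.393 one-sided and 0.443 two-sided. The noncentral t gives 0.395 and 0.446.

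6. **False claim of benefit when there is no effect.** One-sided 0.05: 5%. Two-sided 0.05: 0.05 / 2 = 2.5%. The total type I error is 5% in both cases.

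7. **Adjustment for intake CES-D.** The effective effect is d / √(1 − r²). The document gives no baseline-outcome correlation r, so a range is assumed (noncentral t, 80 per arm):

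| Assumed r | Effective d | Power, two-sided 0.05 | Power, one-sided 0.05 |
|---|---|---|---|
| 0 | 0.350 | 0.595 | 0.712 |
| 0.3 | 0.367 | 0.64 | 0.75 |
| 0.4 | 0.382 | 0.67 | 0.78 |
| 0.5 | 0.404 | 0.72 | 0.82 |
| 0.6 | 0.438 | 0.785 | 0.87 |

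At the same r, the two-sided test has roughly 8 to 12 points less power than the one-sided test. Adjustment helps both and does not remove that gap.

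**The case against.** The strongest reply is that the article gives one-sidedness only as a sample-size input. The Analyses section fixes no test, and a condensed article may leave this to a plan that is not shown. That stands. A reader might infer that the primary outcome will be tested one-sided, but the document does not say so. The consequences for the claim are therefore conditional.

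Three other tempting readings also go too far.

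- *The false-positive risk doubles.* Only the risk of a false claim of benefit doubles. The total stays at 5%.
- *The article calls one-sided testing conventional.* The adjective qualifies the alpha of 0.05, which is a conventional value. The article does not say it of the direction.
- *The Background contradicts the one-sided choice.* It speaks of some older adults, mainly those who focus on negative experiences, and the course is meant to transform those styles. The article also cites favourable meta-analyses and a promising pilot. This is an argument against ruling out worsening, not a contradiction. A two-sided test of means would not detect harm confined to a subgroup either.

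On the number, it could be said that 80 reflects an unstated baseline adjustment: 101 × (1 − 0.45²) = 80.5, so a correlation near 0.45 would give about 81. The article mentions neither adjustment nor correlation, so this cannot be credited to it. It could also be said that slightly over 100 per arm at t0 is close to the 102 needed. However, the article places its requirement at t2, after the 20% loss, and imputing missing outcomes does not restore the lost information.

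**Conclusion.** The point holds in two parts.

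The first does not depend on sidedness. With d = 0.35, 80% power and one-sided alpha 0.05, an unadjusted two-sample t test needs about 102 per arm rather than 80, and 80 per arm gives about 71% power. This rests on the stated inputs and on the absence of any stated adjustment.

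The second is conditional. The trial is sized on a one-sided 0.05 test without a reason, and no other test is stated. If the primary CES-D contrast is judged that way, the risk of falsely claiming benefit is 5% instead of 2.5%, and worsening could not be declared. A two-sided 0.05 test at 80 per arm has about 60% power unadjusted, with a detectable effect of about 0.45 (0.39 one-sided).

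A reader might infer that baseline adjustment makes the change of test free. It does not. Over an assumed correlation of 0.3 to 0.6, two-sided power is about 64% to 79%, below the stated 80% throughout. Setting an adjusted two-sided test against an unadjusted one-sided test is not a like-for-like comparison. The shortfall also should not be blamed on sidedness alone, since part of it exists before sidedness is questioned.

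**What to change.** - Keep the enrolled number; the article describes inclusion as already done.
- State the primary analysis as the between-group CES-D contrast adjusted for intake CES-D, with a two-sided 95% confidence interval, tested two-sided at 0.05 (or, equivalently for a claim of benefit, one-sided at 0.025).
- Correct the Sample size section. On its own one-sided inputs the requirement is about 102 per arm at t2, and 80 per arm gives about 71% power. If 80 came from a calculation with baseline adjustment, state that and give the correlation used.
- Restate power and detectable effect for the test adopted: about 60% and 0.45 unadjusted at 80 per arm, and about 64% to 79% power with adjustment, labelled as resting on an assumed correlation of 0.3 to 0.6.

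Intake CES-D is already collected, so no new data or participants are needed. The cost is wording and a less favourable stated power.
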